## Methods/Design

### Trial design

The trial is designed as a multicenter, randomized, placebo-controlled, two-group, parallel, double-blind superiority trial of 34 participants with an allocation ratio of 1:1.

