### Role of traumatic dental experiences in the etiology and maintenance of dental anxiety

Having undergone an extraction had been found to pose an increased risk for developing persistent anxiety [6, 7, 15]. A small portion of approximately 4 to 8 % of patients suffer from elevated dental trait anxiety or even post-traumatic stress disorder (PTSD) symptoms 1 month after surgical removal of their wisdom teeth [6, 7]. This suggests that the psychological impact of a dental extraction may not be limited to temporary distress but also that a dental extraction is a potential psychologically traumatic experience to at least some patients.

A wide array of studies have shown that dental fear and anxiety are deeply rooted in the experience of previous negative dental or other types of distressing and traumatic life events, for example, [15–18]. A recent case-control study (total n = 153) among dental phobic individuals, subthreshold dental phobics and normal controls, showed that apprehension of dental treatment is strongly associated with the presence of memories of earlier distressing events [19]. For example, 97 % of subthreshold (non)phobic individuals have reported a memory of an aversive event, predominantly in the dental setting, that initiated or exacerbated their dental anxiety; this was significantly higher than the proportion of normal controls reporting such a memory [19]. Emotional disturbance, vividness and sense of reliving of these memories were significantly higher in the subthreshold phobic group and dental phobic group than in the normal controls [19]. Notably, normal controls reported lower levels of intrusiveness and avoidance scores (features typically seen in individuals suffering from PTSD) than both phobic and subthreshold phobic groups (all p values < 0.001). This suggests that the memories of the previous distressing dental events that initiated the dental fear play an important role in the maintenance of the individual’s current anxiety and fear response [19]. This is of importance, as research has indicated that dental anxiety is likely to lead to avoidance of dental care with subsequent adverse effects on oral health status and quality of life [20].

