### Sample size calculation

A power analysis was performed for the primary outcome variable, dental trait anxiety as indexed by the Short-version of the Dental Anxiety Inventory (S-DAI). In order to detect a difference between the propranolol and control condition on changes in dental anxiety scores over time, a two-way (one-within and one-between subjects factor) repeated measures ANOVA will be used. Using G*Power 3.0 software, assuming a correlation of 0.50 between two repeated measurements, a medium size treatment effect (f = 0.25), a power of 0.80, an α significance level of 0.05, and two treatment conditions, the power analysis results in a total sample size of 34 persons.

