### Study outcome measures

Dependent variables were derived from the questionnaires listed below (see Tables 1 and 2).

**Table 1 Tab1:** Primary and secondary study outcome measures

		Measures			
		Primary outcome	Secondary outcomes		
		Trait anxiety (S-DAI)	State anxiety (VAS score)	Vividness/emotional charge (M1) propensity (VAS scores)	Physiological response (HR/BP)
Screening (t = 0)	Screening interview				
Intervention (t = 1)	Preoperative interview	X		X	X
	Postoperative interview		X		
Follow-up (t = 2)	Preoperative interview	X		X	X
	Postoperative interview		X		

*Note:*
*BP* blood pressure, *HR* heart rate, *M1* crucial fear-related memory, *S-DAI* Short version of the Dental Anxiety Inventory, *VAS* visual analog scale

**Table 2 Tab2:** Tertiary outcome measures

		Measures							
		Operative variables/qualitative aspect of the surgical experience (VASs)	Test of blind	IES	FCDS	Qualitative aspect of memory M2 (VASs)	Qualitative aspect of memory M1 (VASs)	Intrusions diary	Specific phobia diagnosis
Screening (t = 0)	Screening interview				X				X
Intervention (t = 1)	Preoperative interview			X			X		
	Postoperative interview	X	X			X		X	
Follow-up (t = 2)	Preoperative interview			X	X	X	X		X
	Postoperative interview	X						X	

*Notes:*
*FCDS* fear of stimuli compromising the dental setting, *IES* Impact of Event Scale - Revised, *M1* crucial fear-related memory, *M2* memory of recent dental extraction procedure, *VAS* visual analog scale

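### The 34 patients enrolled equal the minimum number of complete S-DAI pairs for 0.80 power, while the follow-up S-DAI is collected only from those who attend the second-extraction visit

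*Protocol article*

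**What the plan says.** All places are in the protocol article.

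- **Number enrolled.** Trial design describes a "superiority trial of 34 participants with an allocation ratio of 1:1", that is, 17 per arm. The Abstract gives the same total.
- **Number needed.** Under Sample size calculation, "the power analysis results in a total sample size of 34 persons". The inputs are a within-between repeated measures ANOVA, f = 0.25, "assuming a correlation of 0.50 between two repeated measurements", "a power of 0.80" and "an α significance level of 0.05".
- **When the primary outcome is taken.** Table 1 ("Primary and secondary study outcome measures") marks the S-DAI at two points only: the preoperative interview of the first procedure and that of the follow-up. Second dental extraction procedure makes the follow-up a hospital visit for another extraction, without study medication, with the questionnaires given before and after it. No other route for the S-DAI is described.
- **Who is enrolled.** The Inclusion criteria require high to extreme self-reported fear of tooth or molar removal. The Background states that "research has indicated that dental anxiety is likely to lead to avoidance of dental care".
- **Retention.** The section on adherence and follow-up describes text and email reminders.
- **Analysis.** The Statistical analysis plan section names a condition-by-time repeated measures ANOVA, with baseline as a possible covariate if the arms differ at baseline.

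**The concern.** A power analysis for a change between two time points counts patients who have both measurements. Here that count is also the number to be enrolled, so the stated power holds only if nobody is lost.

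The measurement schedule makes loss plausible. The second S-DAI depends on attending a visit for the procedure that these patients were selected for fearing. Patients whose trait anxiety stays high may be the least willing to come, in which case the missing scores would not be a random subset. Two things are at stake: the chance of detecting the planned effect, and whether those who attend give a fair comparison of the arms.

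**Working it through.** **1. Reproduce the 34.** Inputs from Sample size calculation: f = 0.25, m = 2 measurements, k = 2 groups, correlation ρ = 0.50, α = 0.05. For the within-between interaction in G*Power:

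- noncentrality λ = f² × N × m / (1 − ρ) = 0.0625 × N × 2 / 0.5 = 0.25 × N
- degrees of freedom 1 and N − 2

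N = 34 gives λ = 8.5 and power 0.807. N = 33 gives λ = 8.25 and power 0.795. So 34 is the smallest N reaching 0.80, and the plan's figure is correct as a number of complete pairs.

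Cross-check: the same effect on the change score is d = 2f × √(m / (1 − ρ)) = 0.5 × √4 = 1.0. A two-sample t test with d = 1.0 and 17 per arm also gives 0.807.

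**2. Power if fewer than 34 have both scores.** The document gives no loss rate, so the losses are assumptions. The covariate column uses baseline adjustment at correlation 0.50: residual SD = √(1 − 0.50²) = 0.866, so d = 1 / 0.866 = 1.155, with N − 3 degrees of freedom.

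| Completers | Lost of 34 | Power, planned ANOVA | Power, baseline as covariate |
|---|---|---|---|
| 34 | 0 | 0.807 | 0.90 |
| 33 | 1 (3%) | 0.795 | 0.89 |
| 32 | 2 (6%) | 0.781 | 0.88 |
| 31 | 3 (9%) | 0.77 | 0.87 |
| 29 | 5 (15%) | 0.74 | 0.85 |
| 27 | 7 (21%) | 0.70 | 0.82 |

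Two losses cost 0.807 − 0.781 = 0.026. The shortfall becomes material from about 10% loss.

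**3. Enrolment that would keep 34 complete pairs.** N / (1 − loss): 34 / 0.90 = 37.8, so 38; 34 / 0.85 = 40; 34 / 0.80 = 42.5, so 43 (44 for equal arms).

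**4. Is there bias?** This was simulated under assumptions that are not in the document:

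- SD 1 at each time, correlation 0.50, 17 per arm, completers only
- the log-odds of not attending rise by 0, 1 or 2 per SD of the 4-week score
- overall loss fixed at 20%

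| True effect | Slope | Loss, active v placebo | Estimated effect | Rejection rate |
|---|---|---|---|---|
| 1 SD | 0 (random) | 20% v 20% | 0.995 | 0.695 |
| 1 SD | 1 | 13% v 27% | 0.946 | 0.667 |
| 1 SD | 2 | 10% v 30% | 0.885 | 0.614 |
| 0 | 1 | 20% v 20% | 0.00 | 0.051 |
| 0 | 2 | 20% v 20% | 0.00 | 0.050 |

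Against random loss, the estimate falls by 0.995 − 0.946 = 0.05 SD to 0.995 − 0.885 = 0.11 SD, towards no effect. With no true effect and the same mechanism in both arms there is no bias, and the false-positive rate stays near 0.05.

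**The case against.** The best defence is that the document does not show that patients will stay away. They are already referred and on a surgical waiting list, they consent to a trial with two extractions, and they are reminded of each appointment. The Background statement on avoidance concerns dental care in general. An article also condenses a fuller protocol, and an analysis plan may exist. Rules for missing data, the analysis set and sensitivity analyses may be there, so their absence is not counted here.

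This limits the point but does not remove it. The article itself states that the number needed and the number enrolled are equal, and it fixes when the S-DAI is taken.

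Four stronger readings are tempting and are not supported:

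- **That dropout will bias the comparison.** A reader might infer this from the avoidance statement. Bias needs attendance to depend on follow-up anxiety together with a true drug effect, or a mechanism that differs by arm. Neither is established by the document.
- **That the bias is large.** One might suppose three non-attenders, all in one arm, each 1 SD above those who attend, and read off 3 / 17 = 0.18 SD. That is the shift in a follow-up mean. The planned comparison is of change. At a correlation of 0.50, patients 1 SD higher at follow-up are expected to be 0.5 SD higher at baseline, so the shift is about half, 0.09 SD. Both the 1 SD gap and the one-sided loss would also be invented.
- **That losing one patient defeats the design.** Power falls from 0.807 to 0.795, which is trivial.
- **That the second extraction must be completed.** The S-DAI is scheduled before it. A patient must attend but need not undergo the procedure.

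**Conclusion.** The point holds in a limited form. The 34 is arithmetically right as a count of patients with both scores, but it is used as the enrolment target with no margin, and the only scheduled follow-up S-DAI depends on attending a feared visit.

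Any loss lowers power. The fall is under 3 points for one or two patients; power is then about 0.77 with 31 completers, 0.74 with 29 and 0.70 with 27. These figures assume the plan's own effect size and correlation, an analysis needing both scores (the standard form of the named ANOVA), and loss rates that the document does not supply.

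Bias is a possibility. Where loss depends on follow-up anxiety and the drug works, it is modest and towards no effect, 0.05 to 0.11 SD at an assumed 20% loss. A mechanism that differs by arm could behave otherwise, and the document gives nothing from which to size it. The change is worth making because it is cheap and the trial is still recruiting.

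**What to change.** 1. **Second dental extraction procedure, the adherence section and Table 1:** collect the S-DAI by email or telephone at 4 weeks from every randomised participant who does not attend, or postpones, the second-extraction visit. Include these scores in the primary comparison and record the mode of collection. Cost: one short questionnaire for the few concerned, through email and telephone contact that the trial already uses, and no extra patients. The small downside is that the score is given in a different setting from the preoperative interview, hence the flag.
2. **Sample size calculation:** state that 0.80 requires 34 patients with both S-DAI scores, and give the power at 10-20% loss (about 0.76 to 0.71 with the planned ANOVA). This costs one sentence. If the sponsor prefers to keep 34 complete pairs, enrolment would be 38 at 10% loss, 40 at 15% and 44 in equal arms at 20%.
3. **Statistical analysis plan section:** use the baseline S-DAI as a covariate in every case rather than only when the arms differ at baseline. At a correlation of 0.50 this gives about 0.85 power with 29 completers and 0.82 with 27, which absorbs a 15-20% loss without enlarging the trial. The gain depends on that assumed correlation. The change should be fixed before unblinding.

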### Study population

Adult participants of all genders will be recruited from the waiting list of patients referred to the departments of Oral and Maxillofacial Surgery of the Academic Medical Center of the University of Amsterdam (AMC), the Netherlands, and the department of Oral and Maxillofacial Surgery of the Spaarne Gasthuis Hospital in Haarlem, the Netherlands, by their dentists. Participants have an indication for the removal of at least two teeth and/or molars, and indicate finding a tooth or molar removal highly or extremely anxiety provoking.

### Eligibility criteria

#### Inclusion criteria

The inclusion criteria are as follows:Signed written informed consentMinimum age of 18 years on entry to the studySelf-reported high to extreme fear of tooth or molar removalDutch or English-speaking

#### Exclusion criteria

The exclusion criteria include the following:Asthma or other obstructive pulmonary diseaseCardiac failureCardiac arrhythmiaRenal failureInsulin-dependent diabetes mellitusPregnant or breast-feedingCurrent use of another ß-adrenoreceptor antagonistCurrent use of anxyiolytic or antidepressant medicationCurrently in psychotherapy for dental anxiety Systolic blood pressure < 100 mmHg

### Sample size calculation

A power analysis was performed for the primary outcome variable, dental trait anxiety as indexed by the Short-version of the Dental Anxiety Inventory (S-DAI). In order to detect a difference between the propranolol and control condition on changes in dental anxiety scores over time, a two-way (one-within and one-between subjects factor) repeated measures ANOVA will be used. Using G*Power 3.0 software, assuming a correlation of 0.50 between two repeated measurements, a medium size treatment effect (f = 0.25), a power of 0.80, an α significance level of 0.05, and two treatment conditions, the power analysis results in a total sample size of 34 persons.

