### Evidence for effects of propranolol on dental state anxiety

Currently one randomized, controlled clinical trial (RCT) evaluating the state anxiolytic effects of propranolol in dental phobia has been published. It showed that, as compared to placebo, 80 to 120 mg of oral propranolol significantly diminished self-reported state anxiety during injection of local dental anesthesia (self-reported anxiety about the injection: 5.5 (2.75) versus 7.45 (2.0), p = .033, one-tailed) [41]. A limitation to this study is that follow-up data were lacking. This means that to date, the long-term effects of propranolol on dental trait anxiety are unknown.

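### The sample size section calls its target a medium effect, but f = 0.25 here is a 1.0 SD difference in S-DAI change; power for a 0.5 SD difference is about 0.29

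*Protocol article*

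**What the plan says.** In the Protocol article, the section Sample size calculation bases the trial on the primary outcome, the S-DAI. It aims to detect a difference between arms in change over time, using a repeated measures ANOVA with one within-subject and one between-subject factor, in G*Power 3.0. It states its inputs as "assuming a correlation of 0.50 between two repeated measurements, a medium size treatment effect (f = 0.25), a power of 0.80" and "an α significance level of 0.05". With "two treatment conditions, the power analysis results in a total sample size of 34 persons", the calculation is complete.

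The sections on trial design and primary outcome add 1:1 allocation and two S-DAI measurements, at baseline and at the one-month follow-up. The Statistical analysis plan section names the same condition-by-time ANOVA and brings in the baseline score as a covariate only if the arms differ at baseline. The article gives no S-DAI difference in points and no SD.

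**The concern.** Cohen's labels for f were set for comparisons of group means. With two groups, f = 0.25 corresponds to a standardised difference d = 0.5, and that is how most readers will understand a medium treatment effect. The interaction option in G*Power uses the same letter f for a different quantity, the spread of the interaction cell effects in the arm-by-time table. Here f = 0.25 stands for a difference in change twice as large.

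The section is the only place where the article says what the trial can detect, and no figure in S-DAI points stands beside the label to correct the impression. A reader would take it that a half-SD benefit on trait anxiety has an 80% chance of being found.

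**Working it through.** **Inputs.** From the Sample size calculation section: f = 0.25, correlation r = 0.50, alpha 0.05, power 0.80, two arms. From the primary outcome section: m = 2 measurements. From the trial design section: 1:1 allocation, so 17 per arm. I take all 34 as contributing both measurements.

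**1. Reproduce the plan's figure.** For the within-between interaction, the non-centrality is lambda = f² × N × m / (1 − r), with 1 and N − 2 degrees of freedom.

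- N = 34: lambda = 0.0625 × 34 × 2 / 0.5 = 8.5 on 1 and 32 df, power 0.807.
- N = 32: lambda = 8.0, power 0.781.

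So 34 is the smallest even total that reaches 0.80. Two other readings do not give 34: the between-arm main effect in the same design needs 98, and lambda = f² × N, without the factor m / (1 − r), needs 128. The calculation that was run is therefore clear.

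**2. Translate f into a difference in change.** Let the arms differ in mean change by delta, and let SD be the single-time standard deviation. In a 2 × 2 table the interaction effect in each cell is ± delta / 4, so f = delta / (4 × SD) and delta = 4 × 0.25 × SD = 1.0 SD.

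The SD of change is SD × √(2 × (1 − r)) = SD × √(2 × 0.5) = SD. At r = 0.50 the target is thus 1.0 SD on both the raw-score and the change-score scale.

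**3. Cross-check.** A two-sided t test on change scores with 17 per arm and d = 1.0 has power 0.807, identical to step 1. A simulation of 100,000 trials gave 0.806.

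**4. Power at smaller effects, r = 0.50, N = 34.**

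| Difference in change | Equivalent f | lambda | Power |
|---|---|---|---|
| 1.0 SD | 0.25 | 8.5 | 0.81 |
| 0.8 SD | 0.20 | 5.44 | 0.62 |
| 0.5 SD | 0.125 | 2.125 | 0.29 |

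The simulation at 0.5 SD gave 0.290. For scale, 80% power at 0.5 SD would take 128 patients in total (lambda = 0.015625 × 128 × 2 / 0.5 = 8.0, power 0.801).

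**5. Does another choice rescue the label?**

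- *Baseline as covariate.* The residual SD is SD × √(1 − r²) = SD × √0.75. The non-centrality for 0.5 SD is 0.5 / √0.75 × √(34/4) = 1.68 on 31 df, and power is 0.37.
- *A different correlation, with 0.5 defined on the raw-score SD.* Power is 0.22 at r = 0.3, 0.45 at r = 0.7 and 0.61 at r = 0.8.
- *0.5 defined on the SD of change.* Power is 0.29 whatever r is.

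None of these reaches 0.80. For balance, the power for the plan's own f = 0.25 moves both ways with r: 0.67 at r = 0.3, 0.95 at r = 0.7 and 0.99 at r = 0.8.

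**The case against.** The best defence is that nothing has been miscalculated. The total of 34 follows from the inputs, 0.25 is the conventional medium value of Cohen's f, and the section attaches the word to f. It never mentions d = 0.5. The model, software, correlation, alpha and power are all disclosed, so a statistician can reconstruct the target. All of that stands, and it limits the point to the label. It does not save the label, because the phrase describes a treatment effect in a two-arm trial, and in that sense the design's target is not medium.

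A second objection is that 0.29 is conditional. It holds for a two-sided test of change at r = 0.50 without baseline adjustment. That is fair, and the range has to be shown in both directions, but the conclusion does not turn on it.

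Some stronger readings are tempting and not supported:

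- A reader might infer that the ethics committee was misinformed. It approved the full protocol, version 5, which is not shown.
- A reader might infer that a null result will be taken as evidence against a moderate benefit. The article sets no rule for reading a null result; the abstract and Discussion speak only of a positive one.
- A reader might use the earlier dental trial cited in the Background, "5.5 (2.75) versus 7.45 (2.0), p = .033, one-tailed", to argue that 1.0 SD is out of reach. That figure is state anxiety about an injection, measured on drug. It does not calibrate a four-week change in trait anxiety in either direction.

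**Conclusion.** The point holds as a mislabelled detectable effect. With 34 completers the trial has about 80% power for a 1.0 SD difference between arms in S-DAI change, and about 29% power for the half-SD difference that medium normally denotes (37% with baseline as covariate).

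The result rests on the plan's r = 0.50, a two-sided 5% test, complete data, and the two-group convention that medium means d = 0.5. Over r from 0.3 to 0.8, with d = 0.5 on the raw-score SD, the power of the planned interaction test runs from 0.22 to 0.61.

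A reader might conclude that the sample size is arithmetically wrong or that the primary test is compromised. Neither follows: 34 is correct for the inputs, and the label has no bearing on the test's validity or its type I error.

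**What to change.** In Sample size calculation, replace the effect-size phrase with wording along these lines: a between-group difference in S-DAI change of 1.0 SD (f = 0.25 for the condition-by-time interaction at r = 0.50; a large effect). Add one sentence saying that power for a 0.5 SD difference is about 0.3, or about 0.37 with baseline adjustment.

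The change is to text only. It needs no extra patients and leaves the design, the data collected and the primary test as they are. The cost is that the stated capability becomes less favourable. Giving the target in S-DAI points would help readers, but the article contains no SD from which to derive it, and the correction does not depend on it.

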### Study procedures

The study procedures and participant flow through each stage are summarized in a flow-chart (Fig. 1).

**Fig. 1 Fig1:**
[figure not shown]
Flow-chart of study procedures

#### Screening and recruitment

Potential participants will be recruited from the waiting list of consecutive patients referred to the Department of Oral and Maxillofacial Surgery of the Academic Medical Center of the University of Amsterdam, the Netherlands, and the Department of Oral and Maxillofacial Surgery of the Spaarne Gasthuis Hospital in Haarlem, the Netherlands, by their dentists. The patients have an indication for the removal of at least two teeth and/or molars. They will be contacted by the investigators by telephone, and informed about the trial. After a short introduction, they will be asked to rate how anxiety provoking a tooth or molar removal is to them on a four-point scale (translated from Dutch); “not anxiety provoking at all” (1), “more or less anxiety provoking” (2), “fairly/highly anxiety provoking” (3), or “extremely anxiety provoking” (4). When patients indicate that a score of 3 or 4 applies to them, they will be asked whether they are interested in receiving a potential participant information letter at their home address. The patients will be offered the opportunity to contact an independent physician for questions regarding their participation. No financial or other form of compensation is provided for participation.

